## Abstract

**Background:**

There is limited evidence about vessel wall healing response following implantation of next-generation drug-eluting stents (DES) in patients admitted with a non-ST elevation acute coronary syndrome (NSTE-ACS). Cumulative data indicate that optical coherence tomography (OCT) imaging can optimize percutaneous coronary intervention results and expedite stent endothelialization in the general population but there is lack of data in NSTE-ACS patients.

**Methods:**

The EXPECT study is an investigator-initiated, prospective, randomized trial to assess early vascular healing response following next-generation DES implantation in patients admitted with NSTE-ACS based on OCT guidance and evaluation. Sixty patients are randomized at 1:1:1 ratio to OCT-guided percutaneous coronary intervention (PCI) with 3-month follow-up OCT imaging (O3 group, *n* = 20), to angiography-guided PCI with 3-month follow-up OCT imaging (A3 group, *n* = 20) and to angiography-guided PCI with 6-month follow-up OCT imaging (A6 group, *n* = 20). The primary endpoint of the study is stent strut coverage rate at 3- or 6- month follow-up in the studied groups. The secondary endpoints of the study include OCT imaging endpoints, clinical endpoints, and molecular biology endpoints at the different time points. The clinical endpoints comprised of major cardiovascular adverse events and individual components. The molecular biology endpoints comprised of lipid levels and the levels of inflammatory indicators.

**Discussion:**

The findings of the EXPECT study are anticipated to provide novel insights into vessel wall healing in NSTE-ACS population following implantation of next-generation DES, underscore the value of OCT imaging in expediting strut coverage in this setting, and explore the potential of an early discontinuation of dual antiplatelet therapy (DAPT) in this population.

**Clinical Trial Registration::**

ClinicalTrials.gov, NCT04375319.

## Introduction

Over the past few decades, percutaneous coronary intervention (PCI) has significantly improved clinical outcomes in acute coronary syndrome (ACS) patients. The improved prognosis in this high-risk population has been at least partially attributed to enhanced medical therapy, the broad use of PCI as well as to the introduction of the second-generation drug-eluting stents (DES) that have increased efficacy and high safety profile (1). Current guidelines recommend treatment with dual antiplatelet therapy (DAPT) for 1 year after PCI regardless of stent types (2, 3). However, long-term DAPT may increase the risk of bleeding in the elderly, frail patients and those prone to bleeding with hematological, gastro intestinal, and liver pathologies. DAPT is also associated with a risk of serious bleeding in vulnerable patients with history of falls, previous hemorrhagic cerebrovascular events and can be a limiting factor in patients awaiting elective surgery. In the era of next-generation DES, large-scale randomized studies and meta-analyses have demonstrated that the duration of DAPT can be shortened to 6 months or even to 3 months with no clinical consequences while recent studies currently examine the safety and efficacy of aspirin single antiplatelet therapy post stent implantation (4–7).

In patients admitted with non-ST elevation acute coronary syndrome (NSTE-ACS) that have complex and highly thrombotic lesions, shorter-term DAPT can be considered only in cases of early strut coverage which constitutes a marker of early endothelialization (8). Indeed, cumulative data have underscored the prognostic implications of incomplete strut coverage indicating that this is associated with a high incidence of stent thrombosis (ST) (9) and future major adverse cardiovascular events (MACE) (10–12).

The introduction of optical coherence tomography (OCT) enabled *in vivo* assessment of strut coverage and allow us to calculate vascular repair index (13) and to identify predictors associated with a delayed vessel wall healing. In particular, stent design (i.e., stent polymer, stent strut thickness, and drug elution), strut embedment and apposition, the composition of the underlying plaque, and the time interval between stent implantation and follow-up imaging seem to determine strut coverage (14). Moreover, several studies have shown that in patients with NSTE-ACS the incidence of incomplete strut apposition is greater than in patients with a chronic coronary syndrome while the recently published study (8) has shown that the use of OCT during next-generation stent implantation is associated with a higher incidence of stent embedment and faster endothelialization comparing to angiography-guided PCI. However, most of the recruited patients in this study were suffering from a stable angina. The present investigator-initiated, prospective, randomized trial was designed to investigate the vessel wall healing response following implantation of a next-generation DES with low dose sirolimus elution in NSTE-ACS population and to explore the value of OCT imaging in expediting strut endothelialization.

## Methods and analysis

### Study design

The EXPECT study is an investigator-initiated, prospective, multicenter, randomized clinical trial (www.clinicaltrials.gov, NCT04375319). The objective of this study is to evaluate vessel wall healing response over time in NSTE-ACS patients receiving a next-generation DES implantation, and to examine the value of OCT-guided PCI in expediting stent strut coverage, aiming to underscore the potential of a lower duration DAPT in high bleeding risk population.

### Patient enrollment and randomization

Sixty patients with NSTE-ACS (includes unstable angina pectoris and non-ST segment elevation myocardial infarction) from three centers in Huaihai economic zone (Supplementary Table S1) will be enrolled in this trial. The main inclusion and exclusion criteria are listed in Tables 1, 2, respectively.

**Table 1 tab1:** Inclusion criteria.

1. Male or non-pregnant female aged 18–80 years.
2. Clinical diagnosis of acute non-ST segment elevation myocardial infarction.
3. *De novo* coronary artery lesions. Multiple target lesions should be located in different epicardial vessels.
4. Each target lesion should have a length ≤ 40 mm, and diameter between 2.5–4.5 mm by visual assessment.
5. Target lesion with ≥70% diameter stenosis or ≥ 50% diameter stenosis with myocardial ischemia evident by functional assessment.
6. Each patient is allowed to undergo a maximum of three stent implantations, if necessary (except for bailout stent implantation), each target lesion is allowed to be stented with a maximum of two stents.
7. The coronary anatomy is amenable to PCI.
8. Ability to understand the trial purpose, sign informed consent, and have good compliance with medications.

PCI, percutaneous coronary intervention.

**Table 2 tab2:** Exclusion criteria.

1. Acute ST segment elevation myocardial infarction within the past 1 month.
2. Chronic total occlusive lesion, severe left main stem stenosis, lesions with length > 40 mm, bifurcation lesion requiring double stenting, target vessel diameter > 4.5 mm, and vessels unsuitable for OCT imaging such as severely tortuous vessels and vessels with severe dissection, current infection or any active inflammatory diseases.
3. Non interpretable OCT images.
4. Severe calcific lesions that require treatment with debulking techniques.
5. In stent restenosis lesions.
6. Hemodynamic instability such as cardiogenic shock, or left ventricular ejection fraction <40% (by echocardiography or left ventriculography).
7. Renal impairment: eGFR < 60 ml/(min·1.73 m^2^) or serum creatinine>2.5 mg/dL (178 μmol/L), or patients on hemodialysis.
8. Bleeding tendency, history of active peptic ulcer, history of cerebral hemorrhage or subretinal hemorrhage, history of stroke within the past half year, or contraindications for antiplatelet or anticoagulant treatment.
9. Allergy to antithrombotic medications, contrast agent, or Cobalt Chromium.
10. Life expectancy less than 12 months.
11. Participation in other clinical trial.
12. Poor compliance, unable to provide written informed consent.
13. Heart transplantation.
14. Undergoing chemotherapy or immunosuppressive therapy.
15. Elective surgery requiring stopping anti-platelet therapy within half a year post stent implantation.
16. Platelet count lower than 100 × 10^9^/L, or more than700 × 10^9^/L, and white blood cell lower than 3 × 10^9^/L, liver diseases (such as hepatitis).

OCT, optical coherence tomography; eGFR, estimated glomerular filtration rate

The recruited patients will be randomized at 1:1:1 ratio to three groups using a computer-generated random sequence table. Patients enrolled in the first group will have OCT-guided revascularization and 3-month follow-up OCT imaging (O3 group, *n* = 20), those in the second group angiography-guided PCI and 3-month follow-up OCT imaging (A3 group, *n* = 20) while the patients recruited in the third group angiography-guided PCI and 6-month follow-up OCT imaging (A6 group, *n* = 20).

### Treatment device

All the recruited patients will be implanted with Excrossal (JW Medical Systems, Shandong, China) stent, a novel next-generation sirolimus-eluting stent with a cobalt-chromium alloy and a biodegradable polymer. The dose of sirolimus in this device is reduced to 1/3 of the former product used while the polymer consists of biodegradable polylactic acid. Following stent implantation, the polymer coating degrades into lactic acid, which expedites vascular healing process while the low dose sirolimus elution provides the advantage of accelerating endothelialization without affecting the rate of restenosis (15, 16).

### Treatment and follow-up procedures

In the OCT-guided group, OCT imaging will be performed before PCI to appropriately size stent implantation and following stenting to assess the final results and guide further optimization if needed. A final run will be performed at the end of the procedure to confirm optimal results and exclude common causes of stent failure reported in the literature (17). Patients will be given DAPT (oral aspirin 100 mg once daily, clopidogrel 75 mg once daily, or ticagrelor 90 mg twice daily) and will be put on secondary prevention medications according to the recommended ESC guidelines.

Post discharges all patients will have a follow-up appointment or will be contacted by phone at 1 month, 3 months, 6 months, and 1 year. Subjects assigned to O3/A3 arms will undergo coronary angiography and OCT imaging at 3 months, while those assigned to A6 arm will have invasive assessment and OCT imaging at 6 months after the index procedure (Figure 1). The schedule of enrolment, interventions, and assessments is outlined in Figure 2. The data of each center will be summarized and checked by an independent data monitoring committee.

**Figure 1 fig1:**
[figure not shown]
Study flow chart. NSET-ACS, non-ST elevation acute coronary syndrome; OCT, optical coherence tomography; FLU, follow up; 3 M, 3-month; 6 M, 6-month; and 12 M, 12-month.

**Figure 2 fig2:**
[figure not shown]
Time schedule of enrolment, interventions, and assessments of the study. ECG, electrocardiogram; CCS, Canadian cardiovascular society; OCT, optical coherence tomography; and QCA: quantitative coronary angiography.

### Blood sample measurement

Blood samples (4–5 mL) will be collected from all subjects prior to the procedure and at 12–24 h after the procedure. Blood samples will be also collected at 3 and 6 months follow up. The samples will be centrifuged at 3,000 r/min for 10 min, and the serum obtained will be isolated and stored at −80°C. Serum levels of total cholesterol (TC), low-density lipoprotein (LDL-C), high-density lipoprotein (HDL-C), and triglyceride (TG) will be measured by automatic biochemical analyzer, the pentraxins 3 (PTX-3), vascular cell adhesion molecule 1 (VCAM-1), and matrix metalloproteinase 9 (MMP-9) by enzyme-linked immunosorbent assay, and the high-sensitivity C-reactive protein (hs-CRP) detected by the immune turbidity method.

### QCA and OCT data acquisition and analysis

Intracoronary nitrate will be administered prior to diagnostic angiography in all the recruited patients unless contraindicated due to low blood pressure. Antithrombotic therapy will be administered according to the local protocol prior to insertion of a guidewire in the coronary arteries.

In the angiography-guided group, stent implantation will be performed and optimized with angiography guidance according to local standard practice based on operator’s visual assessment (stent to artery ratio, 1:1). At the end of the procedure, an OCT examination will be performed for research purposes. The collected images will not be available to the operators and these images will be stored and transferred to a dedicated core-lab for image analysis.

In the OCT-guided groups, PCI will be performed under OCT guidance according ILUMIEN III: OPTIMIZE PCI algorithm. The overall procedural approach for OCT-guided stent implantation and post-implant optimization also follows this algorithm (18). In short, the stent size is chosen based on OCT measurement, and post-dilation performed under OCT guidance to achieve fully stent struts apposition and satisfactory stent area (19).

Optical coherence tomography images will be acquired in the culprit vessel and non-culprit vessels using a commercially available C7 or OPTIS imaging system (Abbott, Santa Clara, United States). The imaging catheter will be advanced at least 10 mm distally to the culprit lesion and will be pulled-back using an automated pull-back device under contrast media injection for blood clearance. A second pull-back will be performed in case of long lesions so as the catheter to cover the entire segment of interest.

Repeat coronary angiography and OCT imaging will be also performed at 3- or 6-month follow-up according to the study protocol. The angiographic and OCT imaging data collected at baseline and follow-up will be anonymized and transferred to an independent core laboratory for further analysis.

### Study endpoints

The primary endpoint of the study is the incidence of stent strut coverage (%) at 3- or 6-month follow-up.

The secondary endpoints of the study include angiographic, OCT, and clinical and biomarker outcomes that are listed in Table 3.

**Table 3 tab3:** Endpoints of the trial.

Primary endpoint
The degree of stent struts neointimal coverage (%) at 3 and 6 months
Secondary endpoint
OCT endpoint: Assessed at 3 and 6 months
1. Average and minimal stent diameter, area, and volume.
2. Average and minimal lumen diameter, area, and volume.
3. Average and minimal strut coverage thickness.
4. Strut malposition rate.
5. Vascular repair index.
Clinical endpoints: Assessed at 1, 3, 6, and 12 months
1. Major adverse cardiac events (MACE) composite of cardiac death, target vessel myocardial infarction (TV-MI), and clinical ischemia-driven revascularization.
2. Cardiac death.
3. Non-fatal MI.
4. All revascularization.
5. Target lesion revascularization.
6. Target vessel revascularization.
7. ARC-defined stent thrombosis (early, late, very-late, definite, probable, and possible stent thrombosis).
Molecular biology endpoints: Assessed at baseline, 3 and 6 months
1. Lipid levels (total cholesterol, low-density lipoprotein, high-density lipoprotein, ratio of low-density lipoprotein to high-density lipoprotein, and triglyceride).
2. Molecule indicators (hs-CRP, PTX-3, VCAM-1, and MMP-9).

ARC, academic research consortium; hs-CRP, high sensitive C-reactive protein; PTX-3, pentraxin-3; VCAM-1, vascular cell adhesion molecule-1; and MMP-9, matrix metalloprotein-9.

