Additionally, clinical studies have found that MACE after PCI not only comes from in-stent restenosis or ST in ACS patients but also due to progression of mild to moderately graded disease in the non-culprit vessels as it is a well-known factor that patients presenting with ACS often have multivessel disease (30, 31). A study involving nearly 13,000 ACS patients showed that over 80% of ischemic events occurring after 30 days were unrelated to the culprit lesion that was stented, but were rather spontaneous, or *de novo* events in a non-culprit vessel (32). Intravascular imaging research revealed that non-culprit lesions in ACS patients are often vulnerable plaques, with characteristics such as thin-cap fibroatheroma and those with heavy lipid load. The progress and rupture of these vulnerable plaques in non-culprit vessels can also result in adverse events like thrombosis after PCI (33, 34). Therefore, understanding the evolution of plaque in non-culprit vessels is of great significance to prevent future adverse cardiac events and may potentially influence decision making in the use of DAPT duration. Thus, our study innovatively performs OCT examination in both culprit and non-culprit vessels at baseline and follow-up, to explore vulnerable plaque progression in non-target vessels, measure the changes in the thickness of the fibrous cap over lipid-rich plaques, and examine changes in macrophages accumulations and in the lipid content and in the vulnerable plaques, and their transformation at various time points. Furthermore, plaque progression is usually accompanied with lipid infiltration and inflammatory response. The positive correlation of cholesterol levels, proinflammatory cytokines, and atherosclerotic evolution is well established (35). Stent implantation is associated with vessel wall injury and endothelium disruption while it is well known that strut polymer and drug elution can trigger a pro-inflammatory and hypersensitivity reaction leading to the formation of neoatherosclerotic lesions (34). There are however limited data about the association between vulnerable plaque progression in native segments and neointima proliferation and neoatherosclerotic lesion formation in segments treated with stents. The present study has been designed to provide additional insights and explore the implications of the lipid profile and systemic inflammation assessed by circulatory biomarkers on neointima characteristics and atherosclerotic disease progression in native segments.

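### All, target lesion and target vessel revascularisation have no ischaemia-driven limit, so comparing them with A6 before 12 months can mix treatment effect with the timing of the protocol angiogram

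*Protocol article*

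**What the plan says.** Table 3 (Study endpoints) sets the timing of all clinical outcomes in one line, without distinguishing arms: "Clinical endpoints: Assessed at 1, 3, 6, and 12 months". Within that list, the MACE composite consists of cardiac death, "target vessel myocardial infarction (TV-MI), and clinical ischemia-driven revascularization". The three stand-alone revascularisation items, "4. All revascularization", "5. Target lesion revascularization" and "6. Target vessel revascularization", carry no such restriction.

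The section Treatment and follow-up procedures gives the arms different dates for invasive follow-up. "Subjects assigned to O3/A3 arms will undergo coronary angiography and OCT imaging at 3 months", whereas "those assigned to A6 arm will have invasive assessment and OCT imaging at 6 months after the index procedure". The Discussion adds that "our study innovatively performs OCT examination in both culprit and non-culprit vessels at baseline and follow-up", so the follow-up look goes beyond the stented lesion.

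The section QCA and OCT data acquisition and analysis withholds images from operators only for the OCT run at the end of the index procedure in angiography-guided patients. It says nothing comparable about the follow-up images. Statistical considerations states in general terms that outcomes are compared by chi-squared or Fisher exact test.

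**The concern.** A routine angiogram can lead to a procedure in a patient who would not otherwise have come back for one. An endpoint limited to clinically ischaemia-driven events largely screens such procedures out; an unqualified endpoint counts them. When arms have their routine angiogram on different dates, an unqualified count at an intermediate date depends partly on which arms have already been looked at.

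Here O3 and A3 are looked at three months before A6, so any surveillance effect raises the count in O3 and A3 relative to A6. The O3 versus A6 pairing is the one used in hypotheses 2 and 3, and it bears on the stated interest in shorter DAPT. Readers are likely to look at revascularisation in that pairing as supporting clinical evidence. An excess in O3 that came from the calendar could be misread as a disadvantage of OCT guidance.

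**Working it through.** The plan states no revascularisation rate, power or sample size for these items, so it has no figure of its own to reproduce. The check has two parts.

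**1. Protocol angiograms completed by each assessment.** The inputs are the assessment times in Table 3 and the angiography dates in Treatment and follow-up procedures. The article does not say whether a visit's status is taken before or after the angiogram at that visit, so both conventions are shown.

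| Assessment | Status taken after the angiogram: O3 / A3 / A6 | Status taken before it: O3 / A3 / A6 |
|---|---|---|
| 1 month | 0 / 0 / 0 | 0 / 0 / 0 |
| 3 months | 1 / 1 / 0 | 0 / 0 / 0 |
| 6 months | 1 / 1 / 1 | 1 / 1 / 0 |
| 12 months | 1 / 1 / 1 | 1 / 1 / 1 |

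Under either convention, exactly one of the 3- and 6-month comparisons with A6 is unbalanced. Fixing the cut-off moves the imbalance but does not remove it. O3 and A3 match at every time, and all three arms match at 12 months.

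**2. Possible size at the unbalanced assessment, with no true treatment effect.** The arm size of 20 comes from the protocol. The rates are assumptions: t is the proportion of protocol angiograms that prompt a procedure, and b is the clinically driven rate by that time.

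Counting prompted procedures alone:
- t = 5%: 0.05 × 20 = 1 event in each of O3 and A3, against 0 in A6.
- t = 10%: 0.10 × 20 = 2 events in each, against 0 in A6.
- Fisher exact, two-sided: 1/20 v 0/20 gives p = 1.0. For 2/20 v 0/20, p = 2 × C(20,2)/C(40,2) = 2 × 190/780 = 0.49.
- Against zero events, 5/20 is needed for p < 0.05: 2 × C(20,5)/C(40,5) = 2 × 15,504/658,008 = 0.047.

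Adding a background rate, the expected proportion is b + (1 − b)t in O3 or A3 and b in A6. With b = 1%:

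| t | Proportion in O3 or A3 | Expected events per 20, against 0.20 in A6 | Fisher rejection at two-sided 0.05, 20 v 20 |
|---|---|---|---|
| 0% | 0.010 | 0.20 | about 0% |
| 5% | 0.01 + 0.99 × 0.05 = 0.060 | 1.19 | 0.5% |
| 10% | 0.01 + 0.99 × 0.10 = 0.109 | 2.18 | 4.9% |
| 15% | 0.01 + 0.99 × 0.15 = 0.159 | 3.17 | 16.9% |
| 20% | 0.01 + 0.99 × 0.20 = 0.208 | 4.16 | 34.9% |

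With b = 2% and t from 5% to 20%, the rejection rates are 0.7%, 5.4%, 16.6% and 32.8%. If only ischaemia-driven events count, t is effectively 0 and the expected difference is 0.

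**The case against.** The strongest reply is that no such comparison is planned. Table 3 gives times of assessment, the chi-squared and Fisher sentence is generic, and the three formal hypotheses all concern strut coverage. That stands: a reader might infer a planned test of revascularisation against A6 at 3 and at 6 months, but the article names none. The point applies to any such comparison, descriptive or tested, that the listed times invite.

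A reader might also infer that both time points are biased. Under one consistent counting rule only one of them is, and the article does not say which rule applies.

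A third reply is that event definitions belong in the full protocol or the analysis plan, which are not shown. This is fair as far as missing definitions go, and a narrower definition may exist there. But the point rests on what Table 3 does say: the qualifier is present in one item and absent from three others in the same list, alongside an arm-dependent angiography date.

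Finally, the numbers are small. At 5–10% the expected extra is one or two events, far from significance, so it would be too strong to say that the trial would show a safety difference. This also stands.

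**Conclusion.** The point holds as a modest one about secondary endpoints. Unqualified all, target lesion and target vessel revascularisation can be confounded by surveillance in comparisons with A6 at either 3 or 6 months, depending on whether status is taken after or before the visit's angiogram. The likely direction is an excess in O3 and A3.

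The size rests wholly on an assumed rate of prompted procedures. At 5–10% it is about 1–2 events per 20 against 0, a misleading descriptive gap of 5–10 percentage points that would rarely reach significance. Only at assumed rates of 15–20% does false significance become common (about 17–35%), and nothing in the document suggests that range.

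It would be wrong to extend this to the trial's main conclusions. The strut-coverage endpoint and its sample size do not depend on revascularisation counts. MACE is largely protected by its own wording, O3 and A3 share a schedule, and by 12 months each arm has had exactly one protocol angiogram.

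**What to change.** For Table 3, items 4–6 only:

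- Keep all revascularisation as it is, since a qualifier would change what it means, but report procedures prompted only by the protocol angiogram on a separate line.
- For between-arm comparison, define target lesion and target vessel revascularisation as clinically ischaemia-driven, as MACE already does.
- Base any unqualified comparison with A6 on 12 months, and keep unqualified 3- and 6-month comparisons to O3 versus A3.

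None of this should restrict the timing of comparisons of death, myocardial infarction or stent thrombosis.

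The cost is mainly wording, because MACE already requires a judgement on whether each revascularisation was ischaemia-driven. The price is fewer counted events and no early unqualified revascularisation comparison with A6.
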